## Abstract

**Background:**

Increasing both the frequency and quality of social interactions within treatments for anxiety and depressive disorders in older adults may improve their mental health outcomes and quality of life. This study aims to evaluate the clinical efficacy and cost utility of an enhanced cognitive behavioural therapy (CBT) plus social participation program in a sample of older adults with depression and/or anxiety.

**Methods:**

A total of 172 community-dwelling adults aged 65 years or older with an anxiety and/or depressive disorder will be randomly allocated to either an enhanced CBT plus social participation program (n = 86) or standard CBT (n = 86). Both treatments will be delivered during 12 weekly individual sessions utilising structured manuals and workbooks. Participants will be assessed at pre-treatment, post-treatment, and 12-month follow-up. The primary outcome evaluates mean change in clinician-rated diagnostic severity of anxiety and depressive disorders from baseline to post-treatment (primary endpoint) based on a semi-structured diagnostic interview. Secondary outcomes evaluate changes in symptomatology on self-report anxiety and depression measures, as well as changes in social/community participation, social network, and perceived social support, loneliness, quality of life, and use of health services. Economic benefits will be evaluated using a cost-utility analysis to derive the incremental cost utility ratios for the enhanced CBT program.

**Discussion:**

Outcomes from this study will provide support for the establishment of improved psychosocial treatment for older adults with anxiety and/or depression. Study outcomes will also provide health systems with a clear means to reduce the impact of poor emotional health in older age and its associated economic burden. In addition to the empirical validation of a novel treatment, the current study will contribute to the current understanding of the role of social participation in older adult wellbeing.

**Trial registration:**

Prospectively registered on the Australian New Zealand Clinical Trials Registry (ID: ACTRN12619000242123; registered 19^th^ February 2019) and the ISRCTN registry (ID: ISRCTN78951376; registered 10^th^ July 2019).

## 1. Introduction

### 1.1 Background and rationale

Untreated depression and anxiety in older populations are associated with poor physical health, disability, morbidity, increased costs of service use and medications, as well as greater risk of cognitive decline [1–4]. Furthermore, depressive and anxiety disorders are associated with reduced social participation, poor social support, as well as increased feelings of loneliness and isolation [5–7], which in turn exacerbate risk for suicidal ideation, self-harm, suicide, and death [8–10]. Consequently, the economic costs of these disorders for healthcare systems and society are high [11], especially considering the rapidly ageing population [12].

Anxiety and depression can be successfully treated in older adults using psychological interventions, with the strongest evidence for cognitive behavioural therapy (CBT) [13–15]. In a randomised controlled trial (RCT), adults aged 60 years and older with comorbid anxiety and depression who completed a transdiagnostic CBT program showed large reductions in diagnostic severity for anxiety disorders and unipolar depression compared to a waitlist control condition [16]. In another RCT, this transdiagnostic CBT program also led to faster and sustained improvements in anxiety and depression on diagnostic severity in older adults compared to a discussion group. Furthermore, more than half of participants remitted from their main presenting diagnosis, and almost 40% were remitted from all depressive and anxiety disorders at six months post-treatment [17]. Taken together, these results demonstrate the efficacy of transdiagnostic CBT in reducing anxiety and depression in older adults. However, despite these promising results, up to half of older adults continue to experience clinically impairing symptoms of depression and anxiety following CBT [17].

Poor social connectedness and reduced social participation might be related to suboptimal treatment outcomes. Social participation broadly refers to the degree to which a person participates in society through friendships, social groups, and volunteering [5]. Older adults with anxiety and depression have reduced social participation, poorer levels of perceived social support, and increased feelings of loneliness and isolation [5–7]. Importantly, the relationship between social interactions and emotional distress is likely bidirectional [6]. That is, heightened emotional distress may exacerbate cardinal symptoms of anxiety and depression, such as irritability, avoidance of social interactions, social withdrawal, anhedonia, and negative cognitive biases, which can lead to reduced or unsatisfying social interactions [18]. In turn, heightened sensitivity to social rejection as a result of poor social functioning could also maintain symptoms of anxiety and depression [5, 19, 20].

Despite the evidence and theory linking reduced social participation with the maintenance of anxiety and depression, few studies have examined the impact of directly targeting social factors (social network, relationship satisfaction) on mental health outcomes in older adults. A short-term behavioural activation delivered using videoconferencing has been found to be associated with greater improvements in social connectedness at 12-week follow-up compared to a control group which delivered supportive visiting (without direct coaching of specific coping skill development) also delivered via videoconferencing [21]. Another intervention that focused on addressing psychosocial barriers, including low social self-efficacy and environmental barriers, has shown potential benefits in reducing loneliness in older adults compared with a no-treatment control group [19]. To date, no studies have directly evaluated the effect of targeting the broader concept of social participation, including participation through friendships, social groups, and volunteering, or the impact of targeting this alongside traditional treatment approaches for mental ill-health (e.g., CBT). It is possible that standard treatments for anxiety and depression in older adults would benefit from a more direct and targeted focus on increasing social participation compared to standard CBT intervention.

## 2. Materials and methods

### 2.1 Objectives

The main aim of this study is to evaluate the clinical efficacy and cost utility of an augmented psychological CBT intervention for treating anxiety and/or depression in older adults. We will compare this augmented psychological intervention, which will incorporate a targeted focus on increasing social participation (enhanced CBT), with the current best practice transdiagnostic CBT program (standard CBT) for older adults with anxiety and/or depression [16, 17]. To evaluate the efficacy of the enhanced CBT program, the inclusion criteria for study participants will be selective; participant adherence will be closely monitored through clinician supervision, and the clinicians delivering treatment will be specially trained in the intervention and its application. The intervention will be conducted in our research laboratory and the risk of other confounding interventions (e.g., concurrent treatments) will be limited. The enhanced CBT program has the potential to increase recovery rates for older adults suffering from depressive and anxiety disorders, enhance wellbeing and social participation in this age group, and improve economic outcomes for payers and society. The results of this study could improve the efficacy of psychological interventions for late-life anxiety and depression, in a way that offers value-for-money and could be considered for public financing. In addition, we will examine the underlying moderators of treatment response, and changes in cognitive functioning over time.

### 2.2 Trial design

This study uses a parallel-group superiority randomised controlled trial design to evaluate the clinical efficacy and cost utility of an enhanced CBT program that will comply with the procedures outlined in the CONSORT statement and its extensions, and the Standard Protocol Items: Recommendations for Interventional Trials [SPIRIT; 22]. Eligible participants who provide informed consent are randomly assigned to one of two groups using 1:1 allocation: the control group (Standard CBT) or the intervention group (Enhanced CBT). See Fig 1 for a SPIRIT schedule of enrolment, interventions, and assessments.

**Fig 1 pone.0269981.g001:**
[figure not shown]
SPIRIT schedule of enrolment, interventions, and assessments. *-t1 = Baseline assessment. NOTE: GAI-20 = Geriatric Anxiety Inventory-20 items; GDS-30 = Geriatric Depression Scale-30 items; DSI-S = Depressive Symptoms Inventory–Suicide Subscale; ADIS-5 = The Anxiety Disorders Interview Schedule 5th edition; DJGLS-1 1 = De Jong Gierveld Loneliness Scales-11 items; LSNS = Lubben Social Network Scale; ACPQ-12 = Australian Community Participation Questionnaire-12 items; PID-5–BF = The Personality Inventory for DSM-5 Brief Form; HAq-II = Helping Alliance Questionnaire; AQoL = Assessment of Quality of Life; iPCQ = iMTA Productivity Cost Questionnaire. ^a^Measures will be administered over the phone, online or paper based (participant’s choice).

### 2.3 Study setting

The trial will run through the Macquarie University Centre for Emotional Health Clinic (CEHC), Sydney, Australia. The CEHC has built a strong reputation for psychological treatments and a wide referral base over the past 15 years. In particular, the CEHC has developed a growing reputation for the treatment of older adult anxiety and depression over the past seven years and has a regular referral flow of patients.

### 2.4 Eligibility criteria

Eligible participants are adults aged 65 years or older with a primary diagnosis of an anxiety and/or unipolar depressive disorder according to the Diagnostic and Statistical Manual of Mental Disorders– 5^th^ Edition (DSM-5) [23] criteria assessed by the Anxiety Disorders Interview Schedule for DSM-5 (ADIS-5) [24]. In addition, participants will need to have adequate understanding of the English language as indicated by the ability to read a local newspaper.

Individuals will be excluded if they have current psychotic or bipolar traits, active suicidal intent, significant uncorrected hearing loss and likely moderate to severe dementia as screened by the six-item Cognitive Impairment Screener [25]. Participants currently using psychotropic medications (e.g., anxiolytic and antidepressant medication) will not be excluded, but participants will need to be stabilised on medications for one month before baseline assessment. Participants will report medication type, dosage and frequency of use, and whether the medications were prescribed for management of depression or anxiety. All medication changes will be noted at each assessment and those related to anxiety and mood management will be statistically controlled in analyses.

### 2.5 Interventions

Both the standard and enhanced CBT programs are guided by structured manuals for therapists and supported by workbooks containing homework exercises and lesson summaries for participants. In both treatment conditions, sessions will be run by clinical psychologists and provisional psychologists trained in delivery of the treatment protocols. To control for therapist differences, all therapists will be trained in and will conduct both treatments (allocated randomly). Supervision will be provided by chief investigators (CIs) and associate investigators (AIs) with treatment adherence and differentiation between conditions as a core focus. All therapy sessions will be recorded, and a random 20% will be rated by an independent expert unaware of the study hypotheses for adherence to the therapeutic manual using a codebook and form based on Waltz, Addis, Koerner, & Jacobson [26]. Therapy alliance will be measured using the 19-item Helping Alliance Questionnaire [HAq-II; 27].

The standard program will comprise our empirically validated CBT program for older age anxiety and depression, *Ageing Wisely*. The *Ageing Wisely* program consists of 12 weekly individual one-hour sessions to teach practical skills to help manage anxiety and depression including: goal setting, activity scheduling, problem solving, graded exposure, cognitive restructuring, and sleep hygiene. Skills such as assertive communication training, as well as examples that illustrate application of CBT skills to increase social connections, were not included in the standard CBT program. Homework activities are assigned to promote skill acquisition and generalisation.

The enhanced CBT program also comprises 12 weekly individual one-hour sessions, teaching the same CBT skills as the standard *Ageing Wisely* program in addition to assertiveness training, however all skills include a strong focus and application to bolstering social participation and connections. Specifically, the importance of bolstering social connections is highlighted in treatment rationale. Participants will be encouraged to 1) include regular social activities in activity scheduling; 2) apply cognitive restructuring to shift unrealistic cognitions relating to social situations and interpersonal relationships; 3) reduce avoidance of social situations or being unassertive through the practice of graded exposure; 4) apply problem-solving to overcome barriers to participating in social activities; and 5) practise assertive communication skills to reduce interpersonal conflict. It should be noted that the addition of assertiveness training and other social intervention does not reduce the overall provision of CBT to participants in the enhanced CBT condition. Rather, these skills will be taught in the context of CBT, in that participants are encouraged to identify and challenge maladaptive cognition specifically with respect to social interaction, reduce avoidance of social participation or being non-assertive, and problem-solve any barriers to practising assertive communication. Further explicit skills are taught to increase formation of new social relationships and participate in new social group activities.

### 2.6 Outcomes and participant timeline

The study has a longitudinal design conducted over 12 months with three assessment points. Outcome measures will be collected at baseline (T1) (prior to randomisation); post-treatment (T2) (14 weeks from baseline assessment); and 12-month follow-up (T3) (12 months from start of therapy) by blinded assessors. The primary and secondary outcome measures are presented in Table 1. Measures include self-reported measures and measures administered by an independent assessor (independent clinician) blind to treatment allocation at each of the time points. In addition to blinding of treatment type by the research assistant, at the start of each assessment participants will be asked not to confer the details of their treatment, including treatment condition, to the independent assessors. Clinician-report measures (treating clinician) are also administered.

**Table 1 pone.0269981.t001:** Primary and secondary outcome measures by time interval.

Instrument	Domain	Type^a^	Time Interval^b^^a2^			Reference
			T_1_	T_2_	T_3_	
Demographic Inventory	Demographics	SR	✓	✓	✓	
GAI-20	Anxiety	SR	✓	✓	✓	[28]
GDS-30	Depression	SR	✓	✓	✓	[29]
DSI-S	Depression/Suicide	SR	✓	✓	✓	[30]
ADIS-5	Psychopathology	BA	✓	✓	✓	[24]
DJGLS-11	Social Connection	SR	✓	✓	✓	[31]
LSNS	Social Network	SR	✓	✓	✓	[32]
ACPQ-12	Social Participation	SR	✓	✓	✓	[33]
PID-5 -BF	Personality Traits	SR	✓	✓	✓	[34]
HAq-II	Therapeutic Alliance	SR		✓		[27]
AQoL	Health Related Quality of Life	SR	✓	✓	✓	[35]
Use of Care Services Questionnaire	Cost-Effectiveness	SR	✓	✓	✓	N/A
iPCQ	Cost-Effectiveness	SR	✓	✓	✓	[36]

NOTE: GAI-20 = Geriatric Anxiety Inventory– 20 items; GDS-30 = Geriatric Depression Scale– 30 items; DSI-S = Depressive Symptoms Inventory–Suicide Subscale; ADIS-5 = The Anxiety Disorders Interview Schedule 5^th^ edition; DJGLS-11 = De Jong Gierveld Loneliness Scales—11 items; Lubben Social Network Scale; ACPQ-12 = Australian Community Participation Questionnaire– 12 item; PID-5 –BF = The Personality Inventory for DSM– 5; HAq-II = Helping Alliance Questionnaire; AQoL = Assessment of Quality of Life; iPCQ = iMTA Productivity Cost Questionnaire.

^a^SR = Self-eeport scales administered by participants; OS = Observer scale administered by treating clinician; BA = Scale administered by independent blind assessor

^b^T_1_ = Baseline assessment; T_2_ = 14-week post-treatment assessment; T_3_ = 12-month follow-up assessment.

The primary outcome is the mean changes in Clinical Severity Rating (CSR) across all anxiety and depressive disorders on the ADIS-5 [24] at post-treatment. The ADIS -5 is a semi-structured interview for diagnosing psychiatric conditions according to DSM -5 [23] criteria. The CSR provides an overall severity rating comprising the level of distress and impairment associated with each DSM disorder from 0 (none) to 8 (very severe). A CSR of 4 or higher indicates that the disorder meets or exceeds the threshold for a formal DSM-5 diagnosis. The mean severity rating is calculated to examine overall changes in diagnostic severity over time. This interview will be administered by blinded clinical psychologists, psychologists, or provisional psychologists who will be trained in the interview administration and receive regular supervision to assist with diagnostic decisions.

Secondary outcomes will be measured by:

1) Mean changes in CSR across all anxiety and depressive disorders based on the ADIS-5 at 12-month follow-up.2) Changes in symptomatology at post-treatment and 12-month follow-up on the following measures:**Geriatric Anxiety Inventory** [GAI; 28]. The GAI is a 20-item self-report measure of anxiety in older adults.**Geriatric Depression Scale** [GDS; 29]. The GDS is a 30-item self-report measure of depression for use in older adult populations.**Depressive Symptoms Inventory–Suicide Subscale** [30] is a 4-item measure of suicidal ideation.2) Changes in social participation/connection at post-treatment and 12-month follow-up on the following measures:**De Jong Gierveld Loneliness Scales** [31], which measures feelings of loneliness andperceived social isolation with 11 items.**Lubben Social Network Scale** [LSNS; 32]. The LSNS is a commonly used tool to assess social connections in older adult populations. The 18-item scale assesses the frequency and quality of family, friendship and neighbour support.**The Australian Community Participation Questionnaire-Short Form [33]** The 12-item short form of the ACPQ measures frequency of participation in seven different social activities (contact with extended family, friends and neighbours, contact with friends and family, attending organised community events, volunteering and political protest).3) Cost utility of the interventions on the following measures:**Assessment of Quality of Life** [AQoL-8D; 35, 37]. The AQoL-8D measures quality of life and health outcomes across eight domains (independent living, relationships, mental health, coping, pain, senses, self-worth, and happiness).**Use of Care Services.** The Use of Service survey is developed by the research team to assess use of health and community care services in the preceding six months, including hospital services, medical services, allied health services, community-based services, and diagnostic services, supplemented with linked data from the NSW Centre for Health Record Linkage (CHeReL) on Admitted Patient data, Emergency Department data, and Mental Health Ambulatory data, along with Medicare Benefit Schedule (MBS) and Pharmaceutical Benefit Schedule (PBS) data.**iMTA Productivity Cost Questionnaire** [iPCQ; 36]. The iPCQ is a standardised instrument to measure and value health-related productivity losses including presenteeism and absenteeism in paid and unpaid work.

In addition to the primary and secondary outcome measures, the **Personality Inventory for DSM-5—Brief Form** [PID-5-BF; 34] will be used to undertake a mediation analysis on treatment outcomes. The PID-5-BF is a 25-item self- rated personality trait assessment scale for adults aged 18 years and older. It assesses five personality trait domains including negative affect, detachment, antagonism, disinhibition, and psychoticism, with each trait domain consisting of five items.

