### 2.8 Recruitment

Participants will be recruited to the CEHC from general practices, primary health network, other health professional or health organisations (e.g., aged care, hospital, residential aged care). Participants can self-refer. In addition, the study will be advertised broadly to the community and general practitioners (GPs), using brochures, media and newspaper stories and advertisements, and through Beyond Blue’s professional networks. The GPs in the local area will be informed about the study and provided with a brochure about how to improve detection and screening of anxiety and depression in their older patients.

Following referral, older adults will be screened over the telephone. Intake officers will assess likely suitability for the trial based on the inclusion and exclusion criteria outlined in Section 2.4. Older adults who are likely to meet the inclusion criteria will be sent participant information and consent forms. Intake officers will follow up to review understanding of the participant information and consent forms and to answer any questions. Older adults who are interested in participating will be asked to provide written informed consent, followed by completing full baseline measures according to the study design, including the ADIS administered by clinical psychologists, psychologists, or provisional psychologists at the Macquarie University CEHC. All participants will be allocated a deidentified alpha-numeric code by the research team. If a participant is deemed eligible after completion of the baseline assessment, they will be randomly allocated to one of the two treatment conditions by the research team (see Section 2.9 Assignment of intervention), and an appointment will be scheduled for the first treatment session. The average time between randomisation and entry into therapy is estimated to be two to four weeks depending on participant flow and clinician availability. If an older adult is ineligible for enrolment in the current study, the primary reason of ineligibility will be documented. Participants who do not consent or do not meet eligibility criteria will be offered alternative services at the CEHC as appropriate and/or referred to alternative services in the local area and/or to their GP.

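### The primary post-treatment assessment is timed at 14 weeks from a pre-randomisation baseline, which does not reliably follow 12 weekly sessions that start on average two to four weeks after randomisation

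*Protocol article*

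**What the plan says.** The primary outcome (section 2.6) is the mean change in clinical severity rating on the ADIS-5 at post-treatment, which is T2. The same section times the assessments: "Outcome measures will be collected at baseline (T1) (prior to randomisation"), then "post-treatment (T2) (14 weeks from baseline assessment); and 12-month follow-up (T3) (12 months from start of therapy) by blinded assessors". So T2 is counted from baseline and T3 from the start of therapy. The footnote to Table 1 calls T2 the "14-week post-treatment assessment" and gives no other origin.

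Section 2.8 sets the order of events: "If a participant is deemed eligible after completion of the baseline assessment, they will be randomly allocated to one of the two treatment conditions". It then adds: "The average time between randomisation and entry into therapy is estimated to be two to four weeks depending on participant flow and clinician availability".

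On treatment length, the abstract states: "Both treatments will be delivered during 12 weekly individual sessions utilising structured manuals and workbooks". Section 2.5 confirms 12 weekly sessions for the standard and the enhanced program alike.

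**The concern.** An assessment named post-treatment should come after treatment. Here the 14 weeks start running at baseline, before randomisation and before the wait for a therapist. That wait takes two to four of the 14 weeks on average, and 12 weekly sessions must fit into what is left. If T2 is held to its written date, some participants will be assessed before their last session, and who they are will depend on participant flow and clinician availability.

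What is at stake is the meaning of the primary endpoint. It would combine people who have had the whole program with people still in it. The difference between arms would be measured, in part, before the full content of either program had been delivered, and this would tend to shrink it.

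**Working it through.** **Inputs from the protocol article**
- T2 at 14 weeks from baseline; baseline before randomisation (section 2.6).
- Wait from randomisation to therapy: 2 to 4 weeks on average (section 2.8).
- 12 weekly sessions in both arms (abstract, section 2.5), so session 12 is 11 weeks after session 1 if none is missed.
- d = 0.5, 90% power, two-sided alpha 0.05, 86 per arm (section 2.7).

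**Inputs not given, so assumed**
- Gap from baseline to randomisation: 0, 1 or 2 weeks.
- Spread of individual waits: normal with SD 1 week.

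**The plan's own sample size.** The t-based solution for d = 0.5 is 85.03 per arm, which rounds up to 86 per arm and 172 in total. Power at 86 per arm is 90.3%. The stated figure is reproduced and is not in dispute.

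**Week of session 12, counted from baseline** = gap + wait + 11.

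| Gap (weeks) | Wait 2 | Wait 3 | Wait 4 |
|---|---|---|---|
| 0 | 0+2+11 = 13 | 0+3+11 = 14 | 0+4+11 = 15 |
| 1 (assumed) | 14 | 15 | 16 |
| 2 (assumed) | 15 | 16 | 17 |

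With no gap, 14 minus the week of session 12 is +1, 0 or −1. So T2 is one week after the last session, in the same week, or one week before it with at most 11 of 12 sessions given. Each week of gap, and each postponed session, moves session 12 one week later. If treatment is counted as 12 full weeks, the course ends at gap + wait + 12, which is week 14, 15 or 16 with no gap. T2 at week 14 then fits only the 2-week wait.

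**Share with T2 before session 12.** With no gap and no missed session, this is the probability that the wait exceeds 14 − 11 = 3 weeks. With one extra week of delay, from a gap or one postponed session, the threshold is 2 weeks.

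| Mean wait (SD 1 week, assumed) | No extra delay | One extra week |
|---|---|---|
| 2 weeks | 16% | 50% |
| 3 weeks | 50% | 84% |
| 4 weeks | 84% | 98% |

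**Size of the dilution (illustration).** Suppose the effect is proportional to sessions received and every participant lacks one session at T2. Then d = 0.5 × 11/12 = 0.46, and power at 86 per arm is about 85%. If only half lacked one session, the average would be 11.5/12, d about 0.48 and power about 88%. If everyone lacked two sessions, d = 0.5 × 10/12 = 0.42 and power about 78%; with no gap and a wait in the stated range, that needs a further week of delay.

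**The case against.** The strongest reply is that 14 weeks is a nominal figure. The article calls the visit post-treatment throughout, and the Table 1 footnote does not mention baseline. Staff may in practice wait for the last session, and a visit window may stand in the full protocol, so its absence from an article is no finding. This has some force, but section 2.6 does not leave the origin open: it names the baseline assessment. The same sentence counts T3 from the start of therapy, so the therapy clock was available and was not used for T2. The point is the conflict between a stated origin and a stated wait, not a missing window.

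A second reply is that a fixed interval from a common origin suits intention-to-treat, whereas timing from the first session depends on an event after randomisation. That is right, and it is why a longer fixed interval is also an acceptable remedy.

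Three stronger readings are tempting, and the document supports none of them:
- **That most participants are assessed mid-treatment.** Section 2.8 gives an estimated average, not a distribution. At a 2-week wait with no gap and no missed session, T2 does follow session 12.
- **That the comparison is biased.** Both arms share the same schedule and the same number of sessions, so nothing in the design makes T2 earlier in one arm.
- **That the QALY calculation is compromised by the different origins of T2 and T3.** Section 2.13 does not say how QALYs are accumulated over time, and unequal intervals can be handled with actual dates.

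**Conclusion.** The conflict is certain on the text: a T2 counted 14 weeks from baseline does not reliably follow 12 weekly sessions that begin two to four weeks after randomisation. On the most favourable reading (same-day randomisation, no missed session), the margin runs from one week to spare to one week short.

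How many participants are affected is not known. The 16% to 84% range rests on an assumed SD of 1 week, and the 50% to 98% range adds an assumed week of delay. The effect on the result is probably modest. On the favourable reading, and with waits inside the stated range, the shortfall is about one session at most and is expected equally in both arms. Under proportionality this costs at most about 0.04 in d and about 5 percentage points of power. A larger loss needs a gap before randomisation, postponed sessions or individual waits beyond four weeks. All are plausible, but the article quantifies none of them. The point still matters because it concerns the primary endpoint: as written, that endpoint is not what its name says for every participant.

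**What to change.** Reconcile sections 2.5, 2.6 and 2.8 so that T2 reliably follows a full course, with the therapy schedule unchanged and the same rule in both arms. Either of two routes would do:

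1. Count T2 from the start of therapy, as T3 already is, with a visit window, and use a fixed interval from randomisation for those who never start.
2. Use a longer fixed interval from randomisation. A 4-week wait puts session 12 at 4 + 11 = 15 weeks from randomisation, so the interval must exceed that, with an allowance for longer waits and postponed sessions.

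Recruitment began in July 2019 (section 3.1), so some T2 visits may already have taken place. For these, report by arm the actual time of T2 from randomisation and from the first session, and the number of sessions completed by then. Add a sensitivity analysis of the primary outcome on T2 timing.

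The cost is a short amendment, a changed scheduling rule and a somewhat later T2. The real drawback is that a change made mid-trial leaves two visit timings in one data set. If the sponsor prefers not to accept that, the reporting and the sensitivity analysis are the minimum, together with a plain statement of which origin was used for T2 in practice.
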